### Definitions

In this section we operationalise the definitions and terms to be used throughout this study. Firstly, a key distinction is made throughout this study between grammatical gender (G-gender) and social gender (S-gender). G-gender explicitly refers to the morphology, whereas S-gender indicates a referent, person, or occupational gender expectation. For example, using the masculine generic to refer to a group of *nurses* in Arabic will have masculine G-gender, but social expectations may (or may not) result in a different S-gender interpretation. Importantly, where G-gender information is insufficient or absent, reliance on S-gender information may be utilised to determine the gender of a referent. Additionally, G-gender and S-gender information may be congruent/incongruent, which may induce processing benefits or costs. For example, it may be easier to interpret *engineer* [+ masc] as a man and *nurse* [+fem] as a woman than the other way around. This is because S-gender is typically determined by an individual’s expectations or stereotypical information and is likely to vary due to different socio-cultural backgrounds and personal experiences.

Secondly, when describing a ’male-bias’ in this study, this refers to an over-representation of male referents compared to female referents. Specifically, occurrences of *strict* male interpretations of masculine G-gender, which in principle refers to all S-genders will be considered a male-bias in perception/interpretation. This is to be distinguished from cultural and social biases or attitudes individuals may hold that cannot be attributed to G-gender. Additionally, this male-bias can manifest itself in processing benefits or costs due to violations/confirmations of S-gender expectations (e.g., processing benefits experienced when G-gender is congruent with S-gender (as in *doctor[+masc]* and *nurse[+fem]*) and processing costs when G-gender is incongruent with S-gender (i.e., *doctor[+fem]* and *nurse[+masc]*).

Thirdly, in this study, the term ’number’ always refers to grammatical number (e.g., singular, dual, or plural) unless otherwise stated.

A final note on social gender: during this study binary interpretations of S-gender are more common given the sociocultural background in Egypt, where nonbinary identities are unrecognised and marginalised in formal and informal contexts.

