### Design

The experiment employs both between and within variation and is randomised through a block design (5 blocks). The first factor, which varies between participants, is the language condition. There are four main language conditions, and one sub-condition: singular masculine generics, singular feminine g- gender, gender inclusive binomial word-pairs, English gender neutral, and plural masculine generics as the sub-condition (see Table 1).

**Table 1 pone.0292936.t001:** Between variation and breakdown of conditions.

Condition		Example
**1.**	Singular generic masculine	مدرس ‘Teacher[+masc]’
**1.1**	Plural generic masculine	مدرسين ‘Teachers[+masc]’
**2**	Singular feminine	مدرسة ‘Teacher[+fem]’
**3**	Gender-inclusive: Feminine/Masculine word-pair	مدرسة/ مدرس ‘Teacher[+fem]/Teacher[+masc]’
**4**	Gender-neutral: English neutral	Teacher

There is one factor that varies within-participant and that is the ‘stereotypicality’ of the role. Role nouns can be associated with men (e.g., *manager*), associated with women (e.g., *nurse*), or neutral (e.g., *student*). All participants are presented with the same 12 role nouns (4 in each stereotype) but in different language conditions.

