The third component explores the effect of an absence of grammatical gender on occupational expectations in a gender-neutral language (English). In this component Egyptian bilinguals and British English monolinguals will complete the experimental task with English stimuli (see Table 4). This component will also be used to explore differences between the occupational expectations of English monolinguals and Egyptian bilinguals. The presence of the English monolingual participants acts as a ‘control group’ for the experiment as they cannot be influenced by G-gender information. All their responses should be driven by their stereotypical expectations of the role nouns presented. On the other hand, the bilingual Arabic/English speaker is expected to behave differently. Bilinguals have been shown to shift their perception of gender by language [8, 33]. In the absence of grammatical gender information, the design may allow us to directly access participants occupational expectations based on social gender. However, participants may also showcase gender ‘carryover effects’ from Arabic grammatical gender instead of relying on social stereotypes. This could be seen in instances where participants consistently describe the referent using masculine morphosyntax (e.g., ‘he’, ‘him’, ‘his’), even when the role stereotype is associated with women (e.g., describing a male nurse, secretary, or dancer), due to the Arabic masculine generic convention.

**Table 4 pone.0292936.t004:** Experimental block for English gender-neutral condition.

Block	Male Stereotype	Female Stereotype	No Stereotype
**Block 5**	Manager	Nurse	Student
	Engineer	Dancer	Singer
	Lawyer	Cleaner	Salesperson
	Doctor	Flight Attendant	Actor

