#### Sample size

As this is a novel experiment, an estimation of the effect size based on the previous literature or pilot data is not possible. Consequently, a power analysis cannot be conducted at this stage. As such, the study will initially target the average sample size (30 participants) per condition in the relevant existing literature. Therefore, at present the sample will consist of at least 30 participants in blocks 1–4, and 30 Egyptian bilinguals plus 30 monolinguals in the English block (total of 180). However, after conducting the pilot we will use the results to conduct a formal power analysis in STATA (power 0.9 and *alpha* 0.1) to check if additional participants are required.

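### The definition of male-bias counts every strictly male reading of a masculine prompt, including for male-stereotyped roles, and no stated contrast separates grammar from stereotype for question 1a

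*Protocol article*

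**What the plan says.** The Definitions section of the protocol article sets out to operationalise terms for the whole study. On male-bias it makes three statements in sequence:

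- In general, "this refers to an over-representation of male referents compared to female referents".
- More specifically, strict "male interpretations of masculine G-gender, which in principle refers to all S-genders will be considered a male-bias in perception/interpretation".
- The sentence that follows sets a condition on what may be counted: "This is to be distinguished from cultural and social biases or attitudes individuals may hold that cannot be attributed to G-gender".

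Question 1a in the Introduction asks whether singular masculine generics create a male bias. Question 1b asks whether participants lean on stereotype or on grammar.

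On design, "All participants are presented with the same 12 role nouns (4 in each stereotype) but in different language conditions", and Table 2 shows each noun once in the masculine, once in the feminine and once as a word-pair across blocks 1–3. English monolinguals are the control group in the third component described under Conditions: "All their responses should be driven by their stereotypical expectations of the role nouns presented".

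The Pre-specified analysis plan makes language condition the fixed effect and explores its interaction with stereotype. Data processing & cleaning lets BIC decide whether interactions stay. The Hypotheses section gives one explicit criterion: if masculine and feminine conditions behave alike, masculine generics are judged not to be generic.

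**The concern.** The second statement cannot deliver what the third requires. A masculine prompt for a male-stereotyped role is read as male if grammar drives the reading, and equally if stereotype does. Counting that reading as male-bias attributes to grammar something the article itself expects without grammar: Table 5 predicts 'man' for male roles in the unmarked English condition, and the Speech production section describes a rival account in which unmarked forms simply follow stereotype. The worked example under Outcomes of interest (manager in the masculine, read as a man) is exactly such an ambiguous case.

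What is at stake is the meaning of the answer to 1a. If male-bias is reported under this definition, readers will take a mixture of stereotype and grammar as the effect of grammatical gender. It also undercuts 1b, which needs the two kept apart.

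**Working it through.** **1. The plan's own figure.** Sample size section: "at least 30 participants in blocks 1–4, and 30 Egyptian bilinguals plus 30 monolinguals in the English block (total of 180". Four Arabic blocks of 30, plus 30, plus 30: 4 × 30 + 30 + 30 = 180. This reproduces.

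**2. Singular masculine prompts (counted from Table 2), as male / female / neutral roles.**
- Block 1: 2 / 1 / 1
- Block 2: 1 / 2 / 1
- Block 3: 1 / 1 / 2

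Each column sums to 4, and 30 × 4 = 120. So there are 120 + 120 + 120 = 360 prompts.

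**3. Count under the rule with no grammatical effect.** Let pM, pF and pN be the probabilities of a strictly male reading for male, female and neutral roles, driven by stereotype only. Expected count = 120 × (pM + pF + pN). The documents give no such rates, and the Sample size section says "a power analysis cannot be conducted at this stage", so these are assumptions. For pM, 0.7 is a loose anchor from the Materials section, where male roles had to target men at least 70% of the time.

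| pM / pF / pN | Count by role | Total of 360 |
|---|---|---|
| 0.7 / 0 / 0.3 | 84 + 0 + 36 | 120 (33%) |
| 0.7 / 0.3 / 0.5 | 84 + 36 + 60 | 180 (50%) |
| 0.8 / 0.2 / 0.5 | 96 + 24 + 60 | 180 (50%) |
| 0.9 / 0.1 / 0.5 | 108 + 12 + 60 | 180 (50%) |
| 0.8 / 0.3 / 0.6 | 96 + 36 + 72 | 204 (57%) |
| 1.0 / 0.3 / 0.5 | 120 + 36 + 60 | 216 (60%) |

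Male roles supply 84 to 120 of these occurrences, for example 84/180 = 47% in the second row and 84/120 = 70% in the first.

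**4. The definition's opening sentence applied to the same data.** In the three 50% rows, if every other reading is female, there are 180 male and 180 female readings, so no over-representation. The second sentence nevertheless records 180 occurrences of male-bias. The two sentences can disagree on identical data.

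**5. A between-condition difference.** For stereotype level s, D(s) = P(strictly male | singular masculine, s) − P(strictly male | comparator, s), on the same nouns. If stereotype alone drives both conditions, D(s) = 0 at every level. That zero depends on the comparator having no effect of its own.

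**6. Masculine against feminine.** The article holds that the feminine cannot be used generically. Suppose the masculine is fully generic with male readings of 80%, 20% and 50% for male, female and neutral roles, and the feminine gives 0%. The differences are 80, 20 and 50 points, averaging (80 + 20 + 50)/3 = 50 points. All of that comes from the feminine form and none from a masculine-induced bias.

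**7. Where the information lies.** At the same rates, a masculine form that wholly fixed the reading would add 20 points for male roles, 50 for neutral and 80 for female. At pM = 1.0, male roles could show nothing.

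**The case against.** The case on the other side is substantial. The sentence sits in a theoretical section, and no planned outcome is a count of male-bias occurrences. Outcomes of interest names a proportion of gendered markers weighted by tensed phrase, plus two derived categorical variables. The models compare language conditions on the same nouns with by-item random effects, so the design contains what a separation needs. A condensed article may also leave the choice of contrast to a fuller plan.

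A reader might go further and infer that 1a will be answered yes from stereotype alone, or that the mixed models are invalid. The documents support neither. No test or threshold on the raw count is stated. The Hypotheses section predicts male readings of masculine prompts whatever the stereotype, and with female-role prompts read as male only 20% of the time that prediction would plainly fail. The masculine–feminine criterion is also worded as similarity between conditions rather than as a difference, so judged across all three stereotypes it would not be met under those rates. It carries no quantity or margin, however, and step 6 shows why the corresponding fixed-effect difference cannot stand in for it.

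It is also fair that the word-pair is not a neutral reference. It displays the feminine form first, is hoped to raise retrieval of female exemplars, and may evoke one man and one woman.

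What remains is narrower. The definition is given in this document as the operational one, it fails the requirement in its own next sentence, and no stated contrast is linked to it or to 1a.

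**Conclusion.** The point holds as a fault of definition and interpretation and should be corrected. It does not invalidate the experiment or its models. The rule scores stereotype-driven readings of male roles as male-bias, and masculine against feminine does not isolate the masculine effect.

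The 360 prompts and the 120/120/120 split follow from Table 2 at 30 participants per block. The 33% to 60% range is illustrative only, because every reading rate is assumed. It should not be read as a forecast, nor as a large excess of male over female readings: several of the assumed sets give parity under the definition's opening sentence if the remaining readings are female.

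**What to change.** - **Definition.** Replace the occurrence rule by: male-bias due to grammatical gender is the between-condition difference in the probability of a strictly male reading for the same nouns.
- **Estimation.** Take it from the planned categorical model, by stereotype, with intervals. This needs the stereotype-by-language interaction, so keep that term for this analysis whatever BIC indicates.
- **Answer to 1a.** Base it mainly on neutral and female-stereotyped roles, where stereotype does not predict 'man'. Do not treat male readings of male-stereotyped masculine prompts alone as evidence of male-bias.
- **Two comparators, each labelled for what it is.** (a) Singular masculine minus bilinguals' English readings: carryover from Arabic would shrink this difference, while the option of a neutral pronoun in English could enlarge it. (b) Singular masculine minus word-pair: describe it as masculine relative to inclusive wording, since the pair may itself raise female or mixed readings.

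The cost is revised wording and contrasts from a model already planned, with no new data. The reported bias may be smaller than a raw count, and neither comparator is a pure stereotype baseline. Precision per stereotype is also limited. With 120 responses per condition treated as independent, which is optimistic given repeated participants and four nouns, 30% against 50% has about 89% power at two-sided 0.05, and 30% against 45% about 67%.

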### Speech production

There is consensus in the existing literature that speech production is prefaced by a series of cognitive processes which include different stages relating to the conceptual sphere and preparation, lexical processing, and lemma selection (this includes syntactic categories such as G-gender and number information), and finally articulation and retrieval of phonological components [13, 14]. However, cross-linguistically the order of these processes remains in question [15], especially in inflectional and grammatically gendered languages such as Arabic.

Focusing on lexical and morphemic processing, studies on morphemic decomposition in Arabic show a reliance on root morphemes and not word pattern morphemes (which include gender, tense, number) in processing and organising lexical information [16]. This would suggest that grammatical gender information is secondary to the root information in lexical processing and selection. Based on these findings, we would expect that interpreting semantic information in the generic form would, like other unmarked languages such as English, conform to interpretations that are congruent with social expectations and stereotype associations. For example, *nurse* would be more likely interpreted as a woman and *doctor* as man. However, what is repeatedly shown in other languages, is that masculine grammatical information is almost always likely to reinforce the masculine to male association and promote the retrieval of male exemplars. Importantly, this relationship is found to hold at the bare noun (BN) level where studies on gender priming effects in Italian, German, and Dutch all show that BNs themselves contain gender information, regardless of gender agreement [17, 18]. These findings have major implications for how we model processing of grammatical gender information especially since previous models, such as the WEAVER ++ model, predict that gender information would only be accessed for the sake of agreement at a later stage in processing [8, 19]. Overall, this context is interesting to explore in Arabic as it offers additional information as to how speakers process grammatical gender.

### Epistemological approach

This study is largely influenced by a poststructuralist and postmodernist narrative, whereby language is not a neutral code, but an active influencer of social organisation [20]. It is broadly linked to the Sapir-Whorf hypothesis on linguistic relativity and determinism, which proposes that linguistic constructs shape our understanding of and interactions with the world [21, 22]. However, it does not set out to explicitly test this hypothesis, as the influence of language on cognition is difficult to distinguish from that of other factors which may have confounding effects on cognition. Instead, this study is designed to deepen and broaden our understanding of the perceptual effects of gender-marked language.

## Materials and methods

This report follows the guidance outlined by Van’t Veer and Giner-Sorolla, Bosnjak *et al*. on preregistration in social psychology [23, 24], and the American Psychological Association’s reporting guidelines for experimental studies (PRP-QUANT).

This study adds a novel experimental method to the existing literature on grammatically gendered languages, processing and perception, as well as speech production. Typically, the existing literature has focused on sentence-evaluation paradigms [see 3] and linguistic expression of gender paradigms [see 25]. In this study, we borrow approaches from speech perception and speech production paradigms to explore the way G-gender is processed and produced in Arabic.

### What is the task?

The experiment examines the effect of grammatical-gender on occupational associations through prompted speech production. This is achieved through a speech production task based on an adaptation of the popular board game ’Taboo’ [26]. The participant’s target is to produce as many words as possible related to the prompt to increase their score, without repeating the prompt word itself. Participants are asked to complete this speech production task with a pre-specified time limit, while repeatedly pressing the spacebar, which will act as an attentional load. Working memory and attention is limited [27, 28]. The attentional load in the task can affect the participant’s speech in various ways [29, 30]. In this experiment, the purpose of the attentional load is to reduce speech planning capabilities, thereby increasing reliance on subconscious associations corresponding to implicit beliefs relating to S-gender and occupation.

Participants will be prompted both audibly and visually, where the target word is initially played and visually remains on the screen until the timer runs out. The auditory prompt is to ensure the correct interpretation of the visual target, while avoiding adding diacritics to the visual primes which could result in confounding effects and slower processing for less ‘obvious’ phonetic interpretations [31]. Un-diacretised words presented on their own or out of context can often be ambiguous between several pronunciations. Context is usually sufficient to disambiguate, and therefore outside of pedagogical contexts, fully diacretised text is highly unusual. The visual prompt will be presented on screen for a duration of 20 seconds.

### Design

The experiment employs both between and within variation and is randomised through a block design (5 blocks). The first factor, which varies between participants, is the language condition. There are four main language conditions, and one sub-condition: singular masculine generics, singular feminine g- gender, gender inclusive binomial word-pairs, English gender neutral, and plural masculine generics as the sub-condition (see Table 1).

**Table 1 pone.0292936.t001:** Between variation and breakdown of conditions.

Condition		Example
**1.**	Singular generic masculine	مدرس ‘Teacher[+masc]’
**1.1**	Plural generic masculine	مدرسين ‘Teachers[+masc]’
**2**	Singular feminine	مدرسة ‘Teacher[+fem]’
**3**	Gender-inclusive: Feminine/Masculine word-pair	مدرسة/ مدرس ‘Teacher[+fem]/Teacher[+masc]’
**4**	Gender-neutral: English neutral	Teacher

There is one factor that varies within-participant and that is the ‘stereotypicality’ of the role. Role nouns can be associated with men (e.g., *manager*), associated with women (e.g., *nurse*), or neutral (e.g., *student*). All participants are presented with the same 12 role nouns (4 in each stereotype) but in different language conditions.

### Conditions

This study can be broken down into three components that help explain experimental blocks and condition allocation in the proposed design. For a detailed breakdown of how participants will be allocated to different blocks based on their characteristics, see Fig 1.

**Fig 1 pone.0292936.g001:**
[figure not shown]
Condition allocation based on participants’ characteristics.

The first component evaluates the effect of Arabic grammatical gender (in the singular) on occupational expectations amongst Egyptian Arabic speakers. In this component, participants are randomly allocated across blocks 1–3 where they are presented with role nouns that vary by language and stereotype condition through a Latin square (see Table 2). Based on this design, 3 different participants are required to complete an observation for one role noun (e.g., *nurse*) in the masculine, feminine, and word-pair conditions. There are several reasons for this choice; firstly, it reduces the chance that participants develop an intuition about the real purpose of the experiment. Secondly, it prevents participants from anticipating the G-gender of the stimuli. Thirdly, this design helps avoid responses that are strictly based on priming patterns and local syntactic consistency [32].

**Table 2 pone.0292936.t002:** Latin square blocks for the singular Arabic conditions.

Block	Male Stereotype	Female Stereotype	No Stereotype
**Block 1**	مدير Manager [+ masc]	ممرضة Nurse [+ fem]	تلميذة/تلميذ Student [+ fem/masc]
	مهندسة/مهندس Engineer [+ fem/masc]	راقص Dancer [+ masc]	مغنية Singer [+ fem]
	محامية Lawyer [+ fem]	مضيفة/مضيف طيران Flight Attendant [+ fem/masc]	ممثل Actor [+ masc]
	دكتور Doctor [+ masc]	عاملة نظافة Cleaner [+ fem]	مسؤولة / مسؤول مبيعات Salesperson [+ fem/masc]
**Block 2**	مديرة/مدير Manager [+ fem/masc]	ممرض Nurse [+ masc]	تلميذة Student [+ fem]
	مهندسة Engineer [+ fem]	راقصة/راقص Dancer [+ fem/masc]	مغني Singer [+ masc]
	محامي Lawyer [+ masc]	مضيفة طيران Flight Attendant [+ fem]	ممثلة/ممثل Actor [+ fem/masc]
	دكتورة / دكتور Doctor [+ fem/masc]	عامل نظافة Cleaner [+masc]	مسؤولة مبيعات Salesperson [+ fem]
**Block 3**	مديرة Manager [+ fem]	ممرضة/ممرض Nurse [+ fem/masc]	تلميذ Student [+ masc]
	مهندس Engineer [+ masc]	راقصة Dancer [+ fem]	مغنية/مغني Singer [+ fem/masc]
	محامية/محامي Lawyer [+ fem/masc]	مضيف طيران Flight Attendant [+ masc]	ممثلة Actor [+ fem]
	دكتورة Doctor [+ fem]	عاملة/عامل نظافة Cleaner [+ fem/masc]	مسؤول مبيعات Salesperson [+ masc]

The second component is considered an exploratory sub-experiment of the first which evaluates the effect of plural masculine generics on the occupational expectations of Egyptian Arabic speakers. The key difference between this component and the former is that this block does not test this relationship in other language conditions (such as feminine plurals or in binomial word-pairs) which would require 3 additional blocks instead of one. This component will be used to explore one key question: do plural masculine generics and singular masculine generics elicit the same male-bias in representation? Importantly, this exploratory sub-experiment has 6 experimental stimuli (in the masculine) compared to the other blocks (see Table 3). This is to ensure a balance of masculine and feminine priming throughout the experiment.

**Table 3 pone.0292936.t003:** Experimental block for the plural masculines.

Block	Male Stereotype	Female Stereotype	No Stereotype
**Block 4**	**مديرين** **Managers [+ masc]**	راقصة Dancer [+ fem]	تلميذة/تلميذ Student [+ fem/masc]
	محامية/محامي Lawyer [+ fem/masc]	**ممرضين** **Nurses [+ masc]**	مسؤولة مبيعات Salesperson [+ fem]
	دكتورة Doctor [+ fem]	**مضيفين طيران** **Flight Attendants [+ masc]**	**ممثلين** **Actors [+ masc]**
	**مهندسين** **Engineers [+ masc]**	عاملة نظافة Cleaner [+ fem]	**مغنيين** **Singers [+ masc]**

The third component explores the effect of an absence of grammatical gender on occupational expectations in a gender-neutral language (English). In this component Egyptian bilinguals and British English monolinguals will complete the experimental task with English stimuli (see Table 4). This component will also be used to explore differences between the occupational expectations of English monolinguals and Egyptian bilinguals. The presence of the English monolingual participants acts as a ‘control group’ for the experiment as they cannot be influenced by G-gender information. All their responses should be driven by their stereotypical expectations of the role nouns presented. On the other hand, the bilingual Arabic/English speaker is expected to behave differently. Bilinguals have been shown to shift their perception of gender by language [8, 33]. In the absence of grammatical gender information, the design may allow us to directly access participants occupational expectations based on social gender. However, participants may also showcase gender ‘carryover effects’ from Arabic grammatical gender instead of relying on social stereotypes. This could be seen in instances where participants consistently describe the referent using masculine morphosyntax (e.g., ‘he’, ‘him’, ‘his’), even when the role stereotype is associated with women (e.g., describing a male nurse, secretary, or dancer), due to the Arabic masculine generic convention.

**Table 4 pone.0292936.t004:** Experimental block for English gender-neutral condition.

Block	Male Stereotype	Female Stereotype	No Stereotype
**Block 5**	Manager	Nurse	Student
	Engineer	Dancer	Singer
	Lawyer	Cleaner	Salesperson
	Doctor	Flight Attendant	Actor

